## **10.6 Reporting to the Ethics Committee**

The sponsor-investigator reports all SAEs for which it cannot be excluded that the events are attributable to the interventions under investigation to the coordinating ethics committee within 15 days. If the SAE occurred at one of the participating trial sites, the sponsor-investigator shall report the event also to the responsible local ethics committee concerned within the same period.

## **10.7 Reporting and Handling of Pregnancies**

Pregnancy is an exclusion criterion for the study. However, if a pregnancy is diagnosed after the accrual (during the treatment or within the first 30 days of the follow-up phase), the continuation and discontinuation of the pregnancy (and the treatment) will be discussed with the patient. Any pregnancy during the treatment phase of the study and within 30 days after the study intervention will be reported to the sponsor-Investigator using the specific pregnancy reporting form within 24 hours. The pregnant partner of the patient participating in this trial will be asked for consent to follow-up the course and outcome of the pregnancy, to document and report any abnormal outcome regarding the mother or the child.

## **10.8 Periodic reporting of safety**

An annual safety report is submitted once a year by the sponsor-investigator to all Ethics Committees involved.

## **11. STATISTICAL METHODS**

### **11.1 Hypothesis and Determination of Sample Size**

The sample size calculation is based on the primary outcome, the VHI at 6 to 24 months (averaged). Based on the literature, we consider the VHI to be comparable between TLM and traditional whole larynx radiotherapy. Therefore, the hypothesis is that there is a difference between TLM and SVCI in regard to VHI. Al-Mamgani et al. reported standard deviations for VHI ranging from 2 to 10 score points. A difference of 8 points between the two groups is regarded as clinically relevant and a conservative standard deviation of 8 points is assumed. Based on a two-sample means test, 34 patients (17 per group) are needed to detect a difference in VHI at a two-sided alpha-level of 0.05 with a power of 80%.

This sample size calculation is conservative. In the analysis, the average change from baseline to the four time points (6, 12, 18, and 24 months) will be modelled and additionally adjusted for the baseline VHI to yield more power.

No statistical criteria for the termination of the trial is defined. No interim analysis for futility or safety will be performed.

### **11.2 Randomization and Stratification**

A probabilistic minimization technique will be used for random treatment allocation between the two treatment arms using a 1:1 ratio. The computer chooses a treatment dynamically, based on the tumor stage (Stage 0 vs. I), and VHI at baseline (<34 vs. ≥34) as two predefined stratification factors.

Allocation will be done via a dedicated website within the clinical trial management system also containing the electronic case report forms. Only system administrators who are otherwise not involved in the trial will have access to the algorithm and stored lists during the recruitment period. Investigators receive the allocation only after registration of a patient. The underlying randomization lists and details of the minimization algorithm will not be disclosed but kept securely at CTU Bern. All these measures will help to ensure concealment of allocation.

### **11.3 Planned Analyses**

A detailed description of data preparation and analysis will be elaborated in a statistical analysis plan (SAP).

#### **11.3.1 Datasets to be analyzed, analysis populations**

The primary analysis will follow the intention-to-treat (ITT) principle, i.e. all patients will be analyzed in the group they were originally assigned to at randomization regardless of any protocol violation.

In the per-protocol (PP) analysis, only patients that adhered to the protocol will be evaluated. Patients not receiving the allocated treatment or violating any of the inclusion criteria will be excluded from this analysis set.

#### **11.3.2 Primary Analysis**

The primary analysis will be based on the ITT patient set. Patient characteristics will be presented in a table, separate by treatment group, as number and percentage, mean and standard deviation, or median and interquartile range, as appropriate.

VHI collected over 24 months will be analyzed using a repeated-measures, linear mixed-effects model with a random intercept for the patients and fixed effects for the baseline value, the treatment group, the time points (categorical), interaction terms between treatment group and time points, and randomization stratification factors. We will present the mean VHI difference between the two groups with associated 95% confidence intervals and p-values over all time points (primary outcome) as well as separate for each time point (secondary outcomes) from this model.

JS, GNE, and SPR are measured on a continuous scale and, therefore, will be analyzed using the same approach as for VHI. Jitter and shimmer are expected to show a log-normal distribution and will therefore be log-transformed before the analysis. If the distributions of the other two outcomes also severely deviate from a normal distribution, the measures will be transformed in an adequate way, e.g. by log-transformation. If normality cannot be achieved, measures will be analyzed using a non-parametric Wilcoxon rank sum test, separate for each time point.

Roughness, breathiness, and hoarseness are each assessed on an ordinal scale ranging from 0 to 3. These measures will be dichotomized into 2/3 versus 0/1 and analyzed using mixed-effects logistic regression with a random intercept for the patients and fixed effects for treatment group, the time points (categorical), interaction terms between treatment group and time points, and randomization stratification factors. We will present the odds ratio with associated 95% confidence intervals and p-values over all time points as well as separate for each time point from this model.

The time-to-event outcome loco-regional control will be evaluated using Kaplan-Meier curves and a Cox model adjusted for the randomization stratification factors.

Treatment toxicity at 2 and 5 years will be summarized descriptively for each group, showing the overall number of events as well as number and percentage of patients with events.

Patients will be censored for toxicity assessment at the time of loco-regional and/or distant tumor recurrence.

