## 7. STUDY POPULATION

### 7.1 Inclusion criteria

1. ECOG performance status 0-1 at the time of registration
2.  $\geq 18$  years of age
3. Baseline assessments and documentation of voice quality by means of VHI, JS, RBH, GNE, SPR
4. Histopathologically confirmed, previously untreated unilateral (cT1a or unilateral cTis) stage 0 or I glottic larynx cancer based on the UICC staging system (8th edition)
5. History and physical examination by treating physician (head and neck surgeon and radiation oncologist) within 28 days prior registration
6. The patient must be expected to withstand both study interventions
7. The patient must have undergone panendoscopy with assessment for the feasibility of transoral exposure for resection. Patients without feasible exposure are not eligible
8. Localization of the tumor should allow resection with a minimum of 2 mm macroscopical margin without extension to the contralateral vocal fold, without partial resection of the arytenoid cartilage and without resection of parts of thyroid cartilage (Cordectomy Type I-IV according to the classification of the European Laryngological Society)
9. Hemoglobin  $\geq 10$  g/dL or 6.2 mmol/L (Note: The use of transfusion to achieve Hgb  $\geq 10$  g/dL is acceptable) within the 28 days prior to accrual
10. Women with child-bearing potential and using effective contraception, and not pregnant and agree not to become pregnant (see section 8.6) during participation in the trial and 30 days after radiotherapy. A negative pregnancy test before inclusion (within 28 days) into the trial is required for all women with child-bearing potential. Men agree not to father a child during participation in the trial and 30 days after radiotherapy.
11. Written informed consent, signed by the patient and the investigator.

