### **11.3.3 Secondary Analyses**

In a secondary analysis, we will analyze all outcomes using the PP patient set. Moreover, we will perform subgroup analyses according to tumor stage (stage 0 vs. I), and VHI at baseline (<34 vs. ≥34).

For RBH, we will also consider a proportional odds logistic regression of the original ordinal outcome. Since the assessment is qualitative and performed by different raters, we will also test for heterogeneity between the raters and include a random intercept for raters in logistic models, if necessary.

Toxicities in both arms will be described and compared with TAME methodology.

Further secondary analyses may be described in the SAP.

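### The main RBH model leaves out the baseline R, B or H score that every patient must have, although the mixed models for the other voice outcomes adjust for baseline

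*Protocol*

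**What the plan says.** Protocol 11.3.2 fixes the main RBH analysis: "These measures will be dichotomized into 2/3 versus 0/1 and analyzed using mixed-effects logistic regression". Besides a random intercept per patient, the model has "fixed effects for treatment group, the time points (categorical), interaction terms between treatment group and time points, and randomization stratification factors". An odds ratio is to be reported overall and at each of the four visits, for each of the three items.

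In the same section the VHI model has the baseline value as a fixed effect, and jitter, shimmer, GNE and SPR are to follow the VHI approach.

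The stratification factors do not supply baseline RBH. Section 11.2 allocates "based on the tumor stage (Stage 0 vs. I), and VHI at baseline (<34 vs. ≥34) as two predefined stratification factors".

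Inclusion criterion 3 (7.1) requires "Baseline assessments and documentation of voice quality by means of VHI, JS, RBH, GNE, SPR", and 11.4 expects complete baseline data for all randomized patients.

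As a secondary analysis, 11.3.3 says of RBH that "we will also consider a proportional odds logistic regression of the original ordinal outcome". It names no covariates for that model.

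**The concern.** Among the voice outcomes, RBH alone has a mixed model without its own baseline, and no reason is given. Section 11.1 justifies adjusting VHI for baseline by the gain in power, and the same reasoning applies to RBH. The covariate costs nothing: it is measured before randomization, mandatory and expected to be complete. This is not a detail left open for the SAP, because the protocol spells out the list of fixed effects.

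What is at stake is precision. RBH is a blinded rating in an open-label trial whose primary endpoint is patient-reported, so it helps in judging whether a VHI difference is mirrored in ratings made without knowledge of the arm. With 17 per arm there is little information to spare. The two-category cut, with the ordinal model only to be considered, adds to the loss.

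**Working it through.** **Inputs from the protocol.** 17 per arm (11.1), "random treatment allocation between the two treatment arms using a 1:1 ratio" (11.2), four follow-up visits and three items (5.2), each scored 0 to 3. No RBH distribution and no baseline-to-follow-up correlation is given, so both are assumed below and shown as ranges.

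**The plan's own figure.** Section 11.1 says "34 patients (17 per group) are needed to detect a difference in VHI at a two-sided alpha-level of 0.05 with a power of 80" per cent, with difference and SD both 8 points. The normal approximation gives 2 × (1.96 + 0.84)² × (8/8)² = 15.7, so 16 per arm. The t test has 78.1% power at 16 and 80.7% at 17 per arm. The figure of 17 reproduces. It was set for VHI, and RBH inherits it.

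**Step 1: terms side by side (11.3.2).**

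| Outcome | Baseline value of that outcome | Treatment, visit, interaction | Strata |
|---|---|---|---|
| VHI | yes | yes | yes |
| Jitter, shimmer, GNE, SPR | yes (VHI approach) | yes | yes |
| R, B, H | **no** | yes | yes |

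**Step 2: what the baseline score would add.** On a linear scale the residual variance falls by the factor 1 − ρ², where ρ is the correlation between the baseline score and the patient's follow-up level. Dividing 17 by that factor gives the equivalent number per arm without adjustment.

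| Assumed ρ | 1 − ρ² | 17 / (1 − ρ²) |
|---|---|---|
| 0.3 | 0.91 | 18.7 |
| 0.5 | 0.75 | 22.7 |
| 0.7 | 0.51 | 33.3 |

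For a logistic model this is only approximate. The relevant ρ is the correlation left after stage and the VHI stratum are in the model, so it may be lower than the raw correlation.

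**Step 3: what the cut costs.** With category probabilities p₀ to p₃ and q = p₂ + p₃, the information of the cut relative to proportional odds is 3q(1 − q) / (1 − Σp³).

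| Assumed % in 0/1/2/3 | q | Ratio |
|---|---|---|
| 50/35/12/3 | 0.15 | 0.3825 / 0.8304 = 0.46 |
| 40/40/15/5 | 0.20 | 0.48 / 0.8685 = 0.55 |
| 25/40/25/10 | 0.35 | 0.6825 / 0.9038 = 0.76 |
| 30/30/30/10 | 0.40 | 0.72 / 0.918 = 0.78 |
| 25/25/25/25 | 0.50 | 0.75 / 0.9375 = 0.80 |

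**Step 4: empty cells.** If an arm has no 2/3 ratings at a visit, or only 2/3 ratings, ordinary maximum likelihood gives no finite odds ratio there. With f(p) = (1 − p)¹⁷ + p¹⁷, the chance is 1 − [1 − f(p_A)][1 − f(p_B)]. At 10% in both arms, f = 0.167 and the chance is 1 − 0.833² = 0.306.

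| Assumed 2/3 rate, A / B | Chance per visit | Expected of 12 odds ratios |
|---|---|---|
| 5% / 5% | 66% | 7.9 |
| 10% / 10% | 31% | 3.7 |
| 10% / 20% | 19% | 2.2 |
| 20% / 20% | 4.5% | 0.5 |
| 30% / 30% | 0.5% | 0.1 |

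**Step 5: illustrative power.** 400 simulated trials per scenario had 17 per arm, four visits, a control distribution of 35/35/20/10%, a latent shift of 0.7 SD and a within-patient correlation of 0.6. The models had no time or strata terms.

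| Model | Power, baseline correlation 0.6 | Power, 0.4 | Rejection under no effect |
|---|---|---|---|
| Binary | 0.525 | 0.502 | 0.068 |
| Binary + baseline | 0.672 | 0.555 | 0.058 |
| Ordinal | 0.612 | 0.642 | 0.095 |
| Ordinal + baseline | 0.845 | 0.722 | 0.070 |

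**The case against.** **RBH is secondary and no bias is shown.** This stands. Neither the primary analysis nor the sample size depends on RBH, and the loss is one of precision only.

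**The ordinal model is already foreseen, and the cut is meaningful.** Section 11.3.3 names it, and the cut separates normal or mild from moderate or severe, as the scale in 9.2.2 is labeled. Putting the cut first is defensible, and handling of sparse cells can be left to the SAP. This stands against treating the ordinal model as a needed correction. It does not answer the missing baseline term, which is absent from the listed effects and not mentioned in 11.3.3.

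**The power figures are not those of the planned model.** This stands. The planned model contains stage and dichotomized baseline VHI. If baseline VHI tracks baseline RBH, part of the simulated gain is already taken. The ordinal model without baseline also rejects too often under no effect (0.095).

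**Two stronger readings are tempting.** A reader might infer that many visit-specific odds ratios will be inestimable. That depends on a 2/3 rate that the protocol does not give: Step 4 runs from 66% per visit to 0.5%. Nor would the missing baseline term cause it, since empty cells come from the cut and the small arms. A reader might also infer that RBH is the main or only blinded check on VHI. Section 9.2.2 has jitter, shimmer, GNE and SPR assessed blind as well.

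Finally, adjustment of the acoustic outcomes is not unconditional: 11.3.2 falls back on a Wilcoxon test per visit if normality cannot be reached. The planned models for them still adjust.

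**Conclusion.** The point holds as a correctable loss of precision. The main RBH model omits a mandatory baseline score that its sister models include, and the stratification factors do not replace it. The size depends on an unknown correlation: the variance factor is 0.91 to 0.51 for assumed correlations of 0.3 to 0.7, on a linear approximation.

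The case for the ordinal scale is weaker, a cheap improvement. It rests on assumed distributions (46% to 80% of the information kept by the cut) and on the possibility that 2/3 ratings are uncommon. Where they are 20% or more in both arms, empty cells are a minor matter. The simulated powers show direction only, because they rest on assumed inputs and a simplified model.

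**What to change.** In 11.3.2, add the baseline value of the respective R, B or H score as a fixed effect in the RBH model, and state the same for the proportional-odds model in 11.3.3. This costs one sentence and no new data.

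As a secondary suggestion, commit to the mixed proportional-odds model on the 0 to 3 scale instead of only considering it, preferably as the main RBH analysis with the 2/3 versus 0/1 model as supportive. Settling the order before analysis also avoids choosing between the two after seeing the data. The price is reliance on proportional odds, and one retained cut cannot fully test that assumption. If visit-specific odds ratios from the binary model are kept, the SAP could name a sparse-data method such as Firth-type penalization.

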| Background and Rationale:      | 
Laser surgery and radiotherapy are well-established standards of care for unilateral stage 0 & I carcinoma in situ (Cais) and squamous cell carcinoma of glottic larynx (SCCGL). Based on meta-analyses, functional and oncological outcome after both treatment modalities are comparable. However, no properly conducted randomized trials comparing these treatments exist. The only such trial with the endpoint of voice quality had to be prematurely closed due to low accrual.
 
The traditional radiotherapy involves the treatment of the whole larynx. Recently, a new radiotherapy technique was introduced by a team of researchers from Netherlands, where the treated target volume consists of involved vocal cord and therefore 8 to 10-fold smaller than the target volumes used for traditional whole larynx irradiation. The treatment is reduced to 16 fractions which corresponds to 3 weeks and a day. The results of a prospective cohort (n=30) with single vocal cord irradiation (SVCI) were compared with the results of a historical prospective cohort previously treated with whole larynx radiotherapy (n=131) in the same institute. The median follow-up was 30 months. The voice handicap index (VHI) at all time points beginning from the 6th week after SVCI was significantly superior to the same time points with conventional radiotherapy. Moreover, a comparable local control with SVCI (100%) vs. conventional radiotherapy (92%) was reported at two years, p=0.24. Based on that, the SVCI technique was implemented as a standard approach for SCCGL in many radiation oncology clinics in the recent years.
 
Based on this information, our main aim is to compare SVCI to Transoral CO2-Laser Microsurgical Cordectomy (TLM) with the main focus of patient-reported voice quality.
 |

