The differences between both treatment modalities have been extensively reported. However, either due to no meaningful difference or due to the heterogeneity in the voice analysis techniques, several studies revealed no significant differences while better voice quality was reported after radiotherapy as compared with TLM in other studies.

The traditional radiotherapy involves the treatment of the whole larynx over a period of 4 to 7 weeks. Recently, a new radiotherapy technique was introduced by a team of researchers from Netherlands, where the treated target volume consists of involved vocal cord and therefore 8 to 10 fold smaller than the target volumes used for traditional whole larynx irradiation. The treatment is reduced to 16 fractions with higher dose per fraction which corresponds to 3 weeks and a day. The results of a prospective cohort (n=30) with single vocal cord irradiation (SVCI) were compared with the results of a historical prospective cohort (n=131) previously treated with whole larynx radiotherapy in the same institute. The median follow-up was 30 months. The voice handicap index (VHI) at all time points beginning from the 6th week after SVCI was significantly superior to the same time points with conventional radiotherapy. Moreover, a comparable local control with SVCI (100%) vs. conventional radiotherapy (92%) was reported at two years, p=0.24. Based on that, the SVCI technique was implemented as a standard approach for SCCGL in many radiation oncology clinics in the recent years, including the centers participating in this clinical trial.

In conclusion, the long-term voice quality and oncologic outcome (survival and local tumor control) are comparable with both TLM and traditional radiotherapy. Furthermore, the new SVCI technique offers a possibly superior long-term voice quality with an at least equal oncologic outcome compared to traditional radiotherapy. With this background, our main aim is to compare SVCI to TLM with the main focus of patient-reported voice quality.

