### Toxicity and Oncological Endpoints

- **Loco-regional control** of SCCGL: Loco-regional control is defined as the time between randomization and biopsy-proven HNSCC recurrence at the head and neck region. Patients without any loco-regional failure until the cut-off point will be censored at the last assessment date.
- **Treatment toxicity** at 2 and 5 years based on CTCAE v.5.0. The list of possible treatment-associated toxicities is provided in the Appendix A. Patients will not be further assessed for toxicity in case of a loco-regional and/or distant tumor recurrence.

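### The adjusted Cox model for loco-regional control asks three coefficients of about 1–3 events at two years and, under a constant hazard, about 3–6 at five years

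*Protocol*

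**What the plan says.** Loco-regional control at 2 and 5 years is a listed secondary outcome (section 5.2) and serves the secondary objective of comparing oncological outcome between arms (section 4.3). Section 9.2.2 counts any biopsy-proven recurrence in the head and neck region, timed from randomization, and adds: "Patients without any loco-regional failure until the cut-off point will be censored at the last assessment date". Section 11.3.2 gives the analysis: "The time-to-event outcome loco-regional control will be evaluated using Kaplan-Meier curves and a Cox model adjusted for the randomization stratification factors". The factors are set in section 11.2, where allocation is "based on the tumor stage (Stage 0 vs. I), and VHI at baseline (<34 vs. ≥34) as two predefined stratification factors". The Cox model therefore carries treatment plus two binary covariates.

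The trial has 34 patients, 17 per arm, sized on VHI alone (section 11.1). No expected number of loco-regional events is stated. The only control rates are in the synopsis and section 3.1, from earlier cohorts: "a comparable local control with SVCI (100%) vs. conventional radiotherapy (92%) was reported at two years". For surgery there is no rate. Section 3.1 says only that surgery and radiotherapy give comparable oncological results. Drop-outs are handled by censoring (section 11.4).

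Section 11.3.2 provides fallbacks for other outcomes, such as a transformation or a rank test when normality fails, but none for sparse events. Section 11.3.4 makes any departure from the planned analysis reportable.

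**The concern.** A Cox coefficient has a finite estimate only if events fall in a way that lets the partial likelihood reach a maximum. If all events are in one arm, or in one level of a stratification factor, the likelihood keeps rising as that coefficient goes to plus or minus infinity. Software then prints an extreme hazard ratio with a meaningless Wald interval and p-value. Every added covariate is another route to this failure.

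The outcome is secondary, but it will stand beside a voice result that may influence the choice between surgery and radiotherapy. An undefined or hugely imprecise hazard ratio with a large p-value invites the reading that control is equal. A switch of method after the events are known would look data-driven.

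**Working it through.** **Inputs.** 17 patients per arm, 1:1 (sections 11.1, 11.2). Two-year local control 100% for SVCI and 92% for conventional radiotherapy (synopsis, section 3.1). Assumptions: TLM 92%; SVCI 100%, 96% or 92%; no drop-out, so the event counts are upper values for each scenario; constant hazard for five years.

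**The plan's own figure.** For a difference of 8 points and an SD of 8, the two-sample t-test at two-sided 0.05 has power 78.1% with 16 per arm and 80.7% with 17. The stated 34 is reproduced. It concerns VHI only.

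**Expected events.** E = 17(1 − S_TLM) + 17(1 − S_SVCI).
- Two years, 92%/100%: 17 × 0.08 = 1.36.
- Two years, 92%/92%: 2 × 1.36 = 2.72.
- Five years, S(5) = S(2)^2.5: 0.92^2.5 = 0.812, and 17 × 0.188 = 3.2 in one such arm, 6.4 in two.

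**Chance that an arm has no event.** At two years, 0.92^17 = 0.242. With 92% in both arms, at least one arm is empty with probability 1 − (1 − 0.242)² = 0.43. At five years, 0.812^17 = 0.029, and 1 − (1 − 0.029)² = 0.057.

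**Whole model.** 1,500 trials per scenario were simulated with exponential times and complete follow-up, and each was checked for a coefficient that diverges. The protocol does not give the prevalence of the two factors; 50%/50%, 20%/50% and 20%/30% were assumed, which produces the ranges below.

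| Two-year control TLM / SVCI | Horizon | Expected events | Events per coefficient | Any coefficient infinite | Treatment coefficient infinite |
|---|---|---|---|---|---|
| 92% / 100% | 2 years | 1.36 | 0.45 | 100% | 100% |
| 92% / 96% | 2 years | 2.04 | 0.68 | 79–88% | 60–62% |
| 92% / 92% | 2 years | 2.72 | 0.91 | 63–80% | 42–46% |
| 92% / 100% | 5 years | 3.20 | 1.07 | 100% | 100% |
| 92% / 96% | 5 years | 4.85 | 1.62 | 36–57% | 20–22% |
| 92% / 92% | 5 years | 6.40 | 2.13 | 14–40% | 5–6% |

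The last column agrees with the closed-form 43% and 5.7%. The gap between the last two columns is what adjustment adds.

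**Sensitivity.** With 85% two-year control in both arms, 5.1 events are expected at two years (17 × 0.15 × 2) and some coefficient is infinite in 27–51% of trials. At five years there are about 11.4 events and the figure is 1–13%.

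**Precision when the fit succeeds.** With 3.2 events per arm at five years, the standard error of the log hazard ratio is about √(1/3.2 + 1/3.2) = 0.79. The 95% limits are then the estimate divided and multiplied by exp(1.96 × 0.79) = 4.7.

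**What an empty arm shows.** With 0 failures in 17 and no censoring, the exact two-sided 95% upper limit for the failure risk is 1 − 0.025^(1/17) = 19.5%.

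**The case against.** A reader might infer that the whole trial will see only one to three events, so that the Cox model will probably fail at every analysis. The documents do not support that. One to three is a two-year count; follow-up runs to 60 months and the outcome is also reported at five years. With 92% in both arms and a constant hazard, the five-year treatment coefficient diverges in only 5–6% of trials, and any coefficient in 14–40%. If recurrences are rare after year two, the five-year count would stay nearer the two-year one; the protocol does not settle this.

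A reader might also infer that the plan yields no usable result on oncological outcome. That is too strong. Kaplan-Meier curves are planned, stay usable with no events, and address control at 2 and 5 years directly. Section 11.3.2 does not prescribe a Wald interval or p-value for this model, and no claim of equivalence is planned.

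The rates are also borrowed. The 92% comes from whole-larynx radiotherapy, not TLM. Both figures are local control, whereas the endpoint also counts other recurrences in the head and neck. The 100% rests on 30 patients; 0 of 30 is compatible with a failure risk up to 1 − 0.025^(1/30) = 11.6%, ignoring censoring. Certain failure at 100% control is one end of a range, not a forecast.

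Finally, a convergence rule is ordinarily left to the SAP, which is not at hand. That would answer a complaint about missing detail. Here the protocol names a specific model, and that choice is the problem. Adjusting for the allocation factors is consistent with the other models in the section, but here there are too few events to carry it.

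**Conclusion.** The point stands as a change that should be made to a secondary analysis; the primary VHI analysis is untouched. The protocol's own rates, with 92% assumed for TLM, give less than one event per coefficient at two years (0.45 to 0.91) and about one to two at five years under a constant hazard. At two years the adjusted model will probably have at least one infinite coefficient: 63–80% with 92% control in both arms, 79–88% with 92%/96%, and certainly if SVCI has no failure. At five years the result depends on SVCI. The model cannot be estimated if SVCI has no failure; with 92% in both arms it is more likely estimable than not, with limits nearly fivefold either side of the estimate. Higher failure rates than those quoted would ease the problem, as the 85% scenario shows.

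**What to change.** In section 11.3.2, or in the SAP with the change declared:
- Make the Kaplan-Meier estimates at 2 and 5 years by arm, and their difference with a 95% confidence interval, the main analysis of loco-regional control. Use an interval that allows for censoring and remains valid when an arm has no event. The Greenwood interval collapses to zero width in that case, and plain exact binomial limits ignore censoring.
- Replace the adjusted Cox model with a Firth-penalized Cox model containing treatment only, with a profile-likelihood confidence interval. State that no hazard ratio is reported if neither arm has an event. At two years that has probability 0.242² = 6% with 92%/92%, and 24% with 92%/100%.
- State that a non-significant difference will not be read as equal oncologic control.

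The cost is a few sentences, with no added data or patients. The downside is that the stratification factors are not adjusted for in this one secondary analysis.
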